**1) Primary**			
QoL at 12 months	Intervention improves QoL from baseline to 12 months	EQ-5D-5L total score differences from baseline to 12 months	Linear regression, correcting for baseline
**2) Secondary**			
QoL at 24 months	Intervention improves QoL from baseline to 24 months	EQ-5D-5L total score differences from baseline to 24 months, mental health question separately	Linear mixed model, interactions between time points and interventions
Depression symptoms		PHQ-9 scores	T-test or ANOVA
Intervention adherence		Proportion of participants completing tests.	Descriptive
Screening experiences	Improvement occurred	Self-reported questionnaire scores after 6 and 24 months	Descriptive statistics, T-test or ANOVA

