### Sample Size

In this study we compare the control group with both combined intervention groups with one-test referral for further diagnosis and treatment, and with multiple-test referral follow-up for further diagnosis and treatment. A total of 1,428 participants are required for the study, utilizing a 2:1:1 randomization scheme. This sample size will provide 80% power to detect a difference corresponding to an improvement of 0.40 in QoL. Additionally, frequent screening is expected to be effective in 40% of participants diagnosed with MDD, with a significance level set at 5% [30, 36–38]. Furthermore, a cumulative incidence of MDD during 12 months of 10% was assumed in our high-risk population [27, 39, 40]. These numbers lead to an expected difference in QoL of 0.016 at 12 months between the screening and control groups. A standard deviation of 0.18 in the score of the EQ-5D-5L in the general population has been expected [30, 41]. In the analysis, adjustments were made for the baseline EQ-5D-5L, assuming a correlation coefficient of 0.8 between the baseline measurement and the measurement at 12 months [42]. The design effect for adjusting for the EQ-5D at baseline is hence 0.36. As a result, calculating the sample size using the design effect for a two-sample t-test indicates that 714 participants are required in the control arm and combined intervention arms. To compensate for the potential 20% loss [43] of follow-up in both arms, we aim to recruit an additional 179 participants for the control arm and 179 participants for the intervention arm (1:1 between both intervention groups). To reach our goal we therefore need to include 1,786 participants in total.

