### Statistical analysis

At baseline, descriptive statistics will be utilized to describe participant characteristics, including demographic variables. This baseline assessment provides a foundation for understanding the distribution of key characteristics across the study groups. The statistical analysis for QoL at 12 months will use a standard linear regression model, correcting for baseline QoL measurements and other determinants. Multiple-testing correction will be applied, with the primary focus on identifying differences after 12 months between the control group and combined intervention groups. The secondary analysis utilizes a linear mixed model, incorporating interactions between time points and interventions to investigate screening effects over various time points. It assumes similar effects for both interventions, while interaction terms assess potential differences between intervention arms. This allows us to capture the nature of participant’s responses to the intervention over time. No missing values are anticipated for both the EQ-5D-5L and the PHQ-9 due to mandatory completion. However, there is a potential for entire questionnaire rounds to be missed, thereby resulting in missing data. To mitigate the impact of potential missing data, we will address it using mixed models. Included in the analysis are explanatory variables such as age, gender, ethnicity and other relevant factors readily available for consideration. Table 1 provides a summary of methods of analysis for each variable.

**Table 1 Tab1:** Variables, measures and methods of analysis

**Variables/outcome**	**Hypothesis**	**Outcome Measures**	**Methods of Analysis**

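### Baseline correction is stated for the 12-month QoL regression but not for the 24-month mixed model; followed as written, the 24-month contrast loses precision that the baseline measurement could supply at no cost

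*Protocol article*

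**What the plan says.** In Table 1 (Statistical analysis), the primary row measures "EQ-5D-5L total score differences from baseline to 12 months" and analyses it by "Linear regression, correcting for baseline". The text of the section agrees: the 12-month analysis "will use a standard linear regression model, correcting for baseline QoL measurements and other determinants".

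The row for QoL at 24 months has a response worded in parallel, "EQ-5D-5L total score differences from baseline to 24 months, mental health question separately". Its method is "Linear mixed model, interactions between time points and interventions". The text describes the mixed model as "incorporating interactions between time points and interventions to investigate screening effects over various time points". It then gives an open-ended list of explanatory variables: age, gender, ethnicity and other relevant factors. Baseline QoL is neither named in that list nor excluded from it.

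The Sample Size section relies on baseline adjustment at 12 months, "assuming a correlation coefficient of 0.8 between the baseline measurement and the measurement at 12 months", and derives a design effect of 0.36 from it. It gives no correlation, effect size or power for 24 months. According to the Procedure section, all arms complete the EQ-5D-5L at baseline and at 6, 12 and 24 months.

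**The concern.** Two neighbouring rows of one table have the same kind of response, and baseline correction is written for only one of them. There are two natural ways to fit the 24-month row as it stands. One is a mixed model on difference scores. The other is a mixed model on the raw scores, with baseline as one of the time points and its mean free in each arm. With complete data, both give the raw difference in change between the arms. That contrast is unbiased under randomisation, but it uses the baseline less efficiently than adjustment does.

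The 24-month outcome is where the article looks for the long-term effect (Objectives and hypothesis), and the Abstract says that long-term results will feed a microsimulation model. The mixed model is also the stated answer to missed questionnaire rounds. Because it is meant "to investigate screening effects over various time points", it can yield a 12-month estimate that differs somewhat from the primary one only because baseline was handled differently. Randomisation is stratified by age, gender and living area but not by baseline QoL, so chance imbalance in QoL is left to the analysis.

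**Working it through.** **Inputs.** All are from the Sample Size section: difference 0.016 (0.40 × 0.40 × 0.10), SD 0.18, correlation r = 0.8 between baseline and 12 months, significance level 5%, power 80%, loss to follow-up 20%. A two-sided test is assumed, since it reproduces the stated number. The SD is taken as equal at baseline and follow-up.

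**Step 1: the plan's own figure.** With baseline adjustment the variance factor is 1 − r² = 1 − 0.64 = 0.36, so the residual SD is 0.18 × √0.36 = 0.108.

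n per group = 2 × (1.960 + 0.842)² × 0.108² / 0.016² = 2 × 7.849 × 0.011664 / 0.000256 = 715.2, rounded up to 716.

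The article states 714, so it reproduces within two participants. With 20% loss, 714 / 0.8 = 892.5, rounded up to 893 per group and 1,786 in total, as stated.

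**Step 2: raw change against adjusted contrast.** The variance factor of a raw change score is 2(1 − r). Its ratio to the adjusted factor is 2(1 − r) / (1 − r²) = 2 / (1 + r), so the loss grows as the correlation falls.

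SE = 0.18 × √(factor × 2/714), and power = Φ(0.016/SE − 1.96). At r = 0.8:

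- adjusted: SE = 0.00572, power 79.9%
- raw change: factor 0.40, SE = 0.00603, power 75.7%; 795 per group would be needed for 80%

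| r | Adjusted factor | Raw change factor | Excess variance | Power, adjusted | Power, raw change |
|---|---|---|---|---|---|
| 0.8 (stated for 12 months) | 0.36 | 0.40 | 11% | 79.9% | 75.7% |
| 0.7 (assumed) | 0.51 | 0.60 | 18% | 65.2% | 58.2% |
| 0.6 (assumed) | 0.64 | 0.80 | 25% | 55.5% | 46.7% |
| 0.5 (assumed) | 0.75 | 1.00 | 33% | 49.2% | 39.0% |

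The power columns carry the 12-month difference of 0.016 and 714 participants per group over to 24 months, with complete data. These are assumptions for illustration. Most of the fall down the table comes from the lower correlation itself. The cost of not adjusting is the gap within each row: 4 to 10 percentage points.

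**Step 3: how far two 12-month estimates could differ.** With complete data the raw and adjusted estimates differ by (1 − r) times the chance difference between arms at baseline. The SD of that quantity is 0.2 × 0.18 × √(2/714) = 0.0019, about 12% of the target difference of 0.016.

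A simulation of 3,000 complete-data trials (714 per group, correlation 0.8, effect 0.016) agreed. Both estimators averaged 0.016, their SDs were 0.0058 (adjusted) and 0.0061 (raw change), their correlation was 0.95, and the SD of their difference was 0.0019.

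**Step 4: does the remedy restore the precision?** Yes. With baseline as a covariate, the factor returns to 1 − r². With baseline as an outcome row, equal arm means at baseline and an unstructured covariance, the complete-data contrast at each visit reduces algebraically to the same adjusted difference.

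**The case against.** The strongest reply is that the article never calls the 24-month model uncorrected. The covariate list is open, the table is a summary, and the wording also fits a model with baseline as a covariate or with baseline means constrained equal. How baseline enters a secondary mixed model is often left to the statistical analysis plan, which is not shown here. This stands to the extent that one cannot say the plan prescribes an uncorrected analysis. It does not remove the contrast between two rows that share a response definition and specify baseline handling for only one.

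A reader might go further and infer that the trial throws away precision on which its sample size depends. The documents do not support that. The correlation of 0.8 and the design effect of 0.36 are tied to 12 months, and that analysis is baseline-corrected.

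A reader might also infer that the plan will produce two different 12-month effects, or a biased one. That is not supported either. Under randomisation with complete data both approaches target the same mean difference, chance baseline imbalance adds variance rather than bias, and the 12-month comparison by linear regression is designated as primary. Nor does the article say that two 12-month estimates will be reported side by side. With missed rounds the two models could differ even if both adjust for baseline, because the mixed model also uses partial data.

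**Conclusion.** The point holds as a minor one about the precision and consistency of a secondary outcome. Followed as written, the 24-month row most naturally gives the raw change contrast. The excess variance is about 11% if the baseline to 24-month correlation is also 0.8, about 18% at 0.7 and 25% at 0.6. The last two correlations are assumptions, and all three figures assume complete data and equal SDs. At a correlation of 0.8 the loss is equivalent to giving up 10% of participants (1 − 0.36/0.40). If the analysts already intend to adjust for baseline, nothing is lost and only the wording needs completing. The powered primary comparison stands.

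**What to change.** In the 24-month row of Table 1 and in the Statistical analysis section, specify a linear mixed model for EQ-5D-5L at 6, 12 and 24 months with baseline EQ-5D-5L and baseline-by-time as covariates. Equivalently, keep baseline as an outcome row and constrain the arm means to be equal at baseline. State that the 24-month contrast of control against the combined intervention groups is taken from this model.

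The cost is one line of wording and a few extra model terms. Baseline EQ-5D-5L is already collected in all arms, so no new data or participants are needed. The change should be made before outcomes are seen. It will not force exact agreement with the primary 12-month regression when rounds are missed, but it removes baseline handling as a reason for disagreement.

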**Methods:**

This study will be a three-arm, parallel randomized control trial (RCT) performed in a multi-ethnic population within the municipality of Rotterdam (the Netherlands). The trial includes two intervention groups that will be screened 4-weekly for MDD for 12 months using the Patient Health Questionnaire (PHQ-9) and a control group who does not receive mobile-based screening for MDD. Participants in the one-test intervention arm will be referred for further diagnosis and treatment, if necessary, after a single positive test score for moderate-severe major depression symptoms (PHQ-9 > 10). Participants in the multiple-test intervention arm will only be referred after three consecutive positive test scores. 1786 eligible participants will be included in the RCT, with 446 and 447 in the one-test and multiple-test referral arms, respectively, and 893 in the control arm. Primary outcome is participants’ QoL after 12 months (EQ-5D-5L). Secondary outcomes include participants’ QoL after 24 months (EQ-5D-5L), evaluating the occurrence and severity of MDD symptoms (PHQ-9), intervention engagement, and identifying public mental health differences based on sociodemographic characteristics, including age, gender, ethnicity, financial situation, educational background, and living area. Long-term results of the RCT will be incorporated into a microsimulation model to determine the long-term benefits, harms, and costs of MDD screening.

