## Methods/design

### Study design and setting

The MOOD (MObile-Based Screening fOr Depression) study is designed as a prospective, randomized controlled multi-arm trial with three parallel groups: a control group and two different intervention groups. We developed the MOOD intervention program by incorporating expertise from various stakeholders, including citizens and experts in mental, digital and public health. After completing a short survey to check for inclusion and exclusion criteria and the digital informed consent procedure, randomization will be performed at the individual level in a 2:1:1: ratio for the control group and the two intervention groups respectively. Participants in the control group will not receive mobile-based screening for MDD, while those in the two intervention groups receive a screening test using the PHQ-9 questionnaire at four-week intervals over a 12-month period. The intervention groups will be divided into two arms. In the one-test referral arm, participants who score positive for moderate to severe depressive symptoms (PHQ-9 score > 10) on a single screening will be referred for further diagnostic evaluation and treatment if necessary. In the multiple-test intervention arm, participants will only be referred for further diagnostic evaluation and treatment after three consecutive positive screenings indicating moderate to severe depressive symptoms (PHQ-9 score > 10). For the screening process in this study, we utilized a Clinical Trial Management System (CTMS) software developed by Your Research [20]. The application enhances efficiency by automating research processes such as data management, workflow optimization, and real-time reporting to ensure consistency and compliance throughout the study. Key features include error reduction, robust data encryption, comprehensive audit trails, ensuring data integrity and regulatory compliance. Participants can use this application at any moment to complete the survey(s). If any questionnaire is not finished after three days, participants will receive a reminder via email or push notification, depending on personal preferences. A second reminder will be sent after ten days. This allows participants to remain engaged and adhere to the study timeline. All study materials, including the website, questionnaires, Patient Information Form (PIF), and Informed Consent (IC) form, will be accessible in six languages: Dutch, English, Turkish, Spanish, Polish, and Arabic and will be provided in B1 language proficiency level. These languages were selected to ensure broad accessibility and inclusivity, reflecting the diverse linguistic backgrounds of the study population. Additionally, the questionnaires themselves will be available in 12 languages to further ensure the validity of the responses across the diverse population. The trial will be conducted by the Department of Public Health at the Erasmus University Medical Center Rotterdam, the Netherlands. The intervention area will focus on Rotterdam, particularly on the Southern part of the city, namely the districts Charlois, Feijenoord, and Ijsselmonde. The population in these districts is ethnically and socioeconomically diverse, with more than 90% having origins outside of Dutch heritage and more than 20% is unemployed [21]. It is expected that in this region there will be an above average prevalence of MDD, which will increase the screening’s potential impact and allow for better measurement [1, 6, 19]. This study is evaluated and approved by the Central Committee on Research Involving Human Subjects (CCMO) of the Netherlands (reference: # NL84280.078.23). The study is registered at the ClinicalTrials.gov Protocol Registration and Results System (ID = NCT05989412).

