### Procedure

Participants will be recruited through different online and offline strategies to encourage citizens’ participation according to different cultural backgrounds. This approach ensures inclusivity and reflects the diverse population we aim to engage in the study. Offline recruitment includes in-person interactions with community members called “key figures”, video promotion, presentations and personally addressing people in public areas. Online recruitment efforts will include websites, social media networks, and local newspapers. By utilizing both digital and physical recruitment strategies, we aim to maximize reach and engagement. Interested individuals can enroll by initiating an application procedure through the study’s website [20], where they will complete an application form to assess eligibility. Eligible participants will then be invited to create a secure personal account and will be provided with a digital patient information form (PIF) and a digital informed consent (IC) form (see Additional file 1). The IC procedure is conducted digitally using Valid Sign, a digital signature platform that enables secure signing of documents online and streamlines the consent process. In line with our aim of ensuring simplicity and accessibility, an invitation email will provide instructions on downloading the Your Research CTMS application to their tablet or smartphone. This application will serve as the primary platform for all study related activities. Results will be sent directly to the server and will be accessible to participants at any time through the app. There will be a variety of platforms provided for additional inquiries about the study procedures including mail, WhatsApp or phone calls. Participants who complete and return the signed e-consent form will be enrolled and randomized in the trial. Depending on their assigned intervention arm, participants will be required to fill in questionnaires, sent via the Your Research app, within two weeks. To ensure adherence, push notifications will be sent to participants who do not complete the questionnaire within 3 days. Participants can choose their preferred notification method, which may include email, SMS, or application notifications. The data collection will run for 24 months. Participants, including those in the control group, will complete the EQ-5D-5L questionnaire via the Your Research CTMS application at baseline (0 months), and at 6, 12, and 24 months. Recruitment will be closely monitored to ensure that the target sample size is achieved. Once the sample size is reached, inclusion will be stopped. Participants will receive compensation at the end of the study based on the number of completed questionnaires, with a maximum of €50 (paid in gift cards). Additional vouchers may be earned by inviting more participants via the app. Participants can withdraw from the study at any time during the trial. To address any logistical or general MDD-related queries, participants can visit the study website [20] or contact the researchers by e-mail or WhatsApp. Additionally, a phone line will be available for inquiries on weekdays, staffed by Erasmus MC MOOD study researchers. To ensure participant safety, the program includes specific measures for addressing potential risks. For example, if questionnaire responses indicate severe depressive symptoms or a risk of self-harm, participants will be immediately directed to appropriate crisis support resources, such as ‘De Luisterlijn’ or ‘113 suicide prevention’ [34]. Additional information on suicide prevention and emergency contacts will be provided as needed, based on the assessment results. These safety measures are crucial for addressing any emerging mental health concerns in real-time, ensuring participant well-being throughout the trail.

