#### Secondary outcome measures

QoL: assessing participants’ QoL at baseline (T0) and post-intervention measurement (T24 months) using EQ-5D-5L total scores. Additionally, the last question of the EQ-5D-5L will be examined separately since it focuses on mental health. The EQ VAS will also be used to capture participants’ self-rated health, providing an additional measure of overall health perception.Symptoms of depression: evaluating the occurrence and severity of MDD symptoms using the nine-item PHQ-9.Screening adherence: the adherence to the screening intervention will be examined by assessing the proportion of participants completing the prescribed tests, aiming to understand the feasibility of the screening strategy.Screening experiences: participants’ experience with the screening strategy will be evaluated through self-reported questionnaires after 6 and 24 months.Population differences: the study will identify differences in MDD symptoms within the population based on social demographic characteristics, including age, gender, ethnicity, education level, living area and financial situation.

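### Table 1 assigns an unadjusted t-test or ANOVA to PHQ-9 scores taken about 13 times per screened participant, while the Statistical analysis text calls for mixed models

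*Protocol article*

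**What the plan says.** **Outcome.** Secondary outcome measures defines the depression outcome as "evaluating the occurrence and severity of MDD symptoms using the nine-item PHQ-9". It gives no time point and no contrast.

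**Analysis in Table 1.** The depression-symptoms row lists PHQ-9 scores as the measure and "T-test or ANOVA" as the method. Its hypothesis cell is empty. The linear mixed model appears in Table 1 only for QoL at 24 months.

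**Analysis in the text.** Statistical analysis describes the secondary analysis as a linear mixed model with time-by-intervention interactions, without naming the outcome. It then discusses missing data for both the EQ-5D-5L and the PHQ-9, accepts that whole rounds may be missed, and states: "To mitigate the impact of potential missing data, we will address it using mixed models". It also says that explanatory variables such as age, gender and ethnicity enter the analysis.

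**Who completes the PHQ-9.** Under Study design and setting, the intervention arms "receive a screening test using the PHQ-9 questionnaire at four-week intervals over a 12-month period", and "Participants in the control group will not receive mobile-based screening for MDD". The Procedure section says: "Participants, including those in the control group, will complete the EQ-5D-5L questionnaire", at 0, 6, 12 and 24 months. No readable sentence assigns a PHQ-9 to controls. The schedule is in Figure 1, which is not shown.

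**The concern.** Two stated methods for one outcome disagree. A t-test or one-way ANOVA takes one value per person. Here each screened participant supplies a series, some rounds will be missed, and a first score is available for adjustment. The Table 1 row does not say which score is tested, between which groups, or with what adjustment. An analyst who follows it literally must choose a round after the fact or pool rounds as if they were independent.

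Occurrence is also left without a method. Both the objectives and the outcome definition name it next to severity. It is a yes/no quantity, and a comparison of mean scores does not estimate it.

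Measuring the occurrence and severity of MDD symptoms is the first secondary objective listed. What is at stake is the precision and validity of the comparison between the one-test and multiple-test arms, and clarity on whether the PHQ-9 is meant to inform any comparison with control.

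**Working it through.** **1. The protocol's own figure.** The article gives no calculation for the PHQ-9. Its only sample-size figure is for the EQ-5D-5L, and it relies on baseline adjustment:

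- Expected difference: 0.40 × 0.40 × 0.10 = 0.016.
- SD 0.18 and baseline correlation 0.8 give a design effect of 1 − 0.8² = 0.36, so the adjusted SD is 0.18 × √0.36 = 0.108.
- n per group = 2 × (1.960 + 0.842)² × 0.108² / 0.016² ≈ 716 (two-sided 5%, 80% power). The stated figure is 714, where power is 79.9%.
- 714 / 0.80 = 892.5, rounded up to 893 per group, or 1,786 in total, as stated.

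The figure reproduces. With the same inputs but no baseline adjustment (SD 0.18), power at 714 per group is 39.0%. This shows what an unadjusted test can cost on the protocol's own assumptions. It is not a PHQ-9 figure.

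**2. Number of PHQ-9 scores.** 52 weeks / 4 = 13 rounds per screened participant (14 if baseline is an extra round).

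**3. Cost of each literal reading of the Table 1 row.** The documents give no PHQ-9 correlation, so r (between baseline and a later score, or between rounds) is assumed to lie between 0.3 and 0.8.

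| Assumed r | Variance of baseline-adjusted relative to plain comparison at one round, 1 − r² | Variance inflation missed if 13 rounds are pooled as independent, 1 + 12r |
|---|---|---|
| 0.3 | 0.91 | 4.6 |
| 0.5 | 0.75 | 7.0 |
| 0.6 | 0.64 | 8.2 |
| 0.8 | 0.36 | 10.6 |

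- *One round, unadjusted.* The test is valid but less precise than the adjusted one, by the ratio in the second column. It also drops everyone who missed that round.
- *Rounds pooled as independent.* The true type I error of a nominal 5% test is 2 × [1 − Φ(1.96 / √(1 + 12r))], which is about 36% at r = 0.3 and 55% at r = 0.8. The document does not state this analysis. The row simply does not exclude it.

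**4. Table 1 against the text.** A plain t-test or ANOVA has no time term, no person-level random effect, no covariates, and no way to use a participant who missed the round tested. The Statistical analysis text promises the first and third of these for the secondary analysis generally, and mixed models for missed rounds where the PHQ-9 is named. Both descriptions cannot hold for the PHQ-9.

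**The case against.** The strongest reply is that Table 1 is introduced as a summary and the text above it already describes mixed models. On that view the repeated measures are not ignored, and the time point and covariates can be left to an analysis plan that is not shown. Much of this stands. A reader might infer from the row that the whole plan ignores baseline and repeated measures, but that is true of the row only. What remains is that the summary names a different method from the text for the same outcome, which is a conflict and not an omission.

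A second reply is that a t-test at one round between randomised arms is valid, and that a single round does not lose most of the information. This also stands. On the same assumptions, the mean of 13 rounds has (1 + 12r)/13 of the variance of one round: 0.35 at r = 0.3 and 0.82 at r = 0.8. The gain from using all rounds is real but shrinks as r rises.

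A third point concerns controls. A reader might infer that no depression comparison with control is possible. The documents do not establish this:

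- Figure 1 is not shown, and its legend has a symbol for one-time measurements.
- The content of the baseline assessment is not itemised.
- The Procedure section says that controls complete the EQ-5D-5L, not that they complete nothing else.
- The EQ-5D-5L mental-health question is already a separate secondary outcome.

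Nor do the objectives tie the PHQ-9 to a contrast with control.

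**Conclusion.** The point holds as a conflict between Table 1 and the Statistical analysis text, with a better method available from data already being collected. If one round is tested without adjustment, a baseline-adjusted comparison would have 0.91 to 0.36 of the variance, for assumed correlations of 0.3 to 0.8. If rounds were pooled as independent, the standard errors would be too small. The 4.6- to 10.6-fold figures show the size of that risk and do not describe a planned analysis. Occurrence has no fitting method in the row.

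On controls, the documents support only this: the readable text names no PHQ-9 for them, so no PHQ-9 contrast with control is specified. Whether one is scheduled depends on Figure 1. The point concerns a secondary outcome and leaves the primary analysis untouched. The entry should be corrected before data are analysed.

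**What to change.** 1. In the depression-symptoms row of Table 1, replace the entry with a linear mixed model on the repeated PHQ-9 scores for the comparison of the two screened arms. Include the first PHQ-9 as baseline, time, arm, arm-by-time and the stratification factors (age, gender, living area). Name the time point or average that carries the main contrast.
2. Add a logistic mixed model for occurrence, defined by the study's PHQ-9 threshold. The article writes that threshold as > 10 under Study design and setting and as ≥ 10 under Evaluation instruments. These must be reconciled first.
3. State whether and when controls complete the PHQ-9. If Figure 1 schedules it, say so in Procedure and include that time point in the model as the screened-versus-control contrast. If not, limit the PHQ-9 outcome to the screened arms, and name the EQ-5D-5L anxiety/depression item as the depression measure for comparison with control.

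The cost is a change of wording in Table 1 and Procedure and slightly more analysis work. No new assessment is needed in any arm.
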